### Study Procedures

All recruitment materials will be delivered in a web-based format with a URL forwarding participants to a screening and informed consent survey hosted on the Webropol platform. First, parents will be presented with an eligibility questionnaire to assess whether they and their children making reference to themselves and their least active child aged between 8 and 12 years, meet the inclusion criteria. Eligible parents will then be presented with information about the study and an informed consent form. Parents who provide informed consent to participate in the study will be prompted to provide their name, contact details, and the name of their least active child, aged between 8 and 12 years, and will be enrolled in the study.

After enrolling in the trial, dyads will be assigned by computerized random-digit generation to 1 of 2 groups: an immediate intervention group that receives the intervention immediately after baseline data collection, or a waitlist control group that will receive the intervention after all outcome data have been collected.

Participants in both groups will be asked to provide outcome data immediately after randomization, 3 months later, and 6 months later. Outcome data will be collected through web-based surveys hosted on the Webropol platform and through physical activity measurement devices mailed to participants’ homes. For web-based surveys, parents will be emailed 2 separate URLs: 1 for themselves and 1 for their child. Parents will be instructed that they may help their child understand the survey items but should avoid influencing their child’s answers to the questionnaire.

Participants in the immediate intervention group will receive the intervention between the baseline and 3-month data collection points, while participants in the waitlist control group will receive the intervention after all data collection has been completed. While data are planned to be collected at baseline, 3 months, and 6 months, the trial includes a stopping rule, such that 6-month follow-up data will not be collected if there is no effect of the intervention on the primary outcome (ie, leisure time physical activity) at the 3-month follow-up. The trial design flow diagram is presented in Figure 1.

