## Methods

### Trial Design

The trial will adopt a randomized waitlist control design in which parent-child dyads are the unit of randomization. Families will be randomized on sign-up to either an intervention group that receives the intervention immediately after baseline data collection or to a waitlist control group that will receive the intervention after all outcome data have been collected.

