### Participant Recruitment and Eligibility

Parent-child dyads will be recruited from the general Finnish population through direct contact with a panel company, through social media advertisements, and through posts on parenting discussion boards and forums. Individuals who responded to the advertisements were directed to a screening survey hosted on the Webropol platform. To be eligible for inclusion, dyads must consist of a parent or guardian aged >18 years and a child aged 8-12 years, and both dyad members need to be considered sedentary. Parents are considered sedentary if they were not active for at least 30 minutes a day on 5 or more days in the past week, and children are considered sedentary if they were not active for at least 60 minutes per day in the past week. Dyads will be excluded if either the parent or child reported having a medical condition or injury likely to prevent them from safely engaging in physical activity. People meeting the inclusion criteria can continue in the Webropol survey to read information about the trial and are then offered the opportunity to provide their contact details to opt-in to the trial.

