### Intervention

#### Immediate Intervention Group

The intervention consists of 4 web-based sessions hosted through a videoconferencing platform (Zoom Inc) and facilitated by 1 or 2 members of the research team. The 4 sessions will be delivered in weeks 1, 3, 5, and 8 of the program. Summaries of each session, including the target constructs and behavior change techniques used in each session, are presented in Table 1. The first session will involve only parents and will last 90 minutes. It focuses on instructing parents in the use of autonomy-supporting parenting behaviors. The remaining 3 sessions will involve both parents and children and will last 45 minutes. Session 2 prompts a discussion of the benefits of an active lifestyle, including enjoyment and importance, and gets participants to set individual and joint physical activity-related goals. Session 3 teaches participants how to make action plans and coping plans (ie, problem-solving) when pursuing physical activity goals. Session 4 covers social norms related to physical activity, has participants specify their identity related to physical activity, and prompts social support strategies within each dyad.

**Table 1 table1:** Content and targets for each intervention session in the ProAct trial. Behavior change techniques preceded by an “M” are drawn from the Motivation and Behavior Change Techniques [38]. Behavior change techniques preceded by a “T” are drawn from the Behavior Change Taxonomy version 1 [39].

Session	Target constructs	Behavior change techniques
Session 1: 90 minutes and parents only	Autonomy supportive parenting	M3. Use non-controlling, informational language M5. Provide a meaningful rationale M6. Provide choice M7. Encourage the person to experiment and self-initiate the behavior M10. Show unconditional regard M12. Use empathic listening M16. Clarify expectations T1.1 Goal setting yeah T1.4 Action planning T4.1 Instruction on how to perform the behavior T4.2 Information about antecedents T5.3 Information about social and environmental consequences T5.6 Information about emotional consequences T8.1 Behavioral practice/rehearsal T16.3 Vicarious consequences

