### Ethical Considerations

All study procedures have been approved by the University of Jyväskylä Human Sciences Ethics Committee (statement number 806/13.00.04.00/2023). All parents interested in participating in the study will be presented with detailed information about the intervention, potential risks to participants, the right to withdraw, and data security arrangements. Parents will have the chance to read this information and ask questions of the research team before providing their informed consent to participate. Data will be stored on secure cloud-based servers hosted by the University of Jyväskylä consistent with our data archiving and storage management plan, compliant with university guidelines. At the conclusion of data collection, participants’ physical activity and data on psychological measures at each measurement point will be matched using pseudonymized codes and deidentified to the greatest extent possible. Participants will not be offered any financial or other compensation for their participation.

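### Dyads are enrolled and randomised once the parent consents, so an unwilling child can be lost after allocation with no baseline data

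*Protocol article*

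**What the plan says.** The protocol article gives one consistent order of events.

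- **Screening.** Study Procedures: "First, parents will be presented with an eligibility questionnaire to assess whether they and their children" qualify. Participant Recruitment and Eligibility sets the criteria: "dyads must consist of a parent or guardian aged >18 years and a child aged 8-12 years, and both dyad members need to be considered" inactive by its definitions, with an exclusion for a limiting condition or injury in either member. The child's willingness is not among them.
- **Consent and enrolment.** Study Procedures: "Parents who provide informed consent to participate in the study will be prompted to provide their name, contact details, and the name of their" child (the least active one in the age range), and enrolment follows. Ethical Considerations describes the same step from the parent's side: "Parents will have the chance to read this information and ask questions of the research team before providing their informed consent to participate".
- **Allocation.** Trial Design: "Families will be randomized on sign-up to either an intervention group" or to the waitlist. Study Procedures: "After enrolling in the trial, dyads will be assigned by computerized random-digit generation to 1 of 2 groups".
- **Baseline.** Study Procedures: "Participants in both groups will be asked to provide outcome data immediately after randomization, 3 months later, and 6 months later". The child's own survey link, sent by email to the parent, and the posted devices belong to this data collection.
- **After baseline.** Immediate Intervention Group, after a first session for parents only: "The remaining 3 sessions will involve both parents and children and will last 45 minutes". Waitlist Control Group: the same data collection and no intervention tasks while it lasts.

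The child is a participant in their own right. The primary outcome is measured in children as well as parents, and the hypothesis in the Discussion covers both.

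**The concern.** As described, the parent's consent is enough to trigger enrolment and randomisation, and nothing asked of the child is described before that. If the child then declines, the dyad is already in an arm and the refusal is a post-allocation loss. Because baseline also follows randomisation, a child who declines at first contact has no child-reported value at any time point. Full-information maximum likelihood, the stated approach to missing data, then has little to work with, and those lost cannot be compared with those retained on the child's own baseline measures.

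The two arms also ask different things of the child during the outcome period: three 45-minute live sessions plus data collection in one, data collection only in the other. If families know the allocation when the child responds, the share of children lost could differ by arm. The comparison exposed is the child part of the primary outcome at 3 months. The article also makes collection of the 6-month data depend on that 3-month effect.

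**Working it through.** **Step 1. The plan's own figures (Power Analysis).** Inputs: f = 0.235, alpha 0.05, power 0.80, 178 participants, 30% attrition.

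- 178 / (1 − 0.30) = 254.3, which matches the stated 254, or 127 dyads.
- The 178 is reproduced by a noncentral F calculation with noncentrality N × f² and two numerator degrees of freedom. That is an inference, since the article does not name the test; one numerator degree of freedom gives 145. This point does not dispute either stated figure.
- On the two-group scale, d = 2 × 0.235 = 0.47.
- The attrition allowance is 0.30 × 127 = 38.1 dyads. It is one overall rate, not split by arm or by timing.

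**Step 2. The sequence.** Parent answers for both members → parent consents and names the child → enrolment → randomisation → outcome data requested, including the child's link and device. The child first appears in the last step.

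**Step 3. Effect on numbers (refusal rates assumed).** Take 63.5 dyads per arm and suppose that a refusing child takes the dyad out. Dyads left = 63.5 × (1 − r_c) + 63.5 × (1 − r_i), where r_c and r_i are the refusal rates in the control and intervention arms. Further loss that still leaves 178 = 1 − 178 / (2 × dyads left).

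| r_c | r_i | Dyads left | Participants | Further loss allowed |
|---|---|---|---|---|
| 5% | 5% | 120.7 | 241.3 | 26.2% |
| 0% | 15% | 117.5 | 235.0 | 24.2% |
| 5% | 15% | 114.3 | 228.6 | 22.1% |
| 10% | 20% | 108.0 | 215.9 | 17.6% |

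The allowance can absorb these losses if other attrition stays within the last column.

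**Step 4. Effect on the comparison (rates and SD gap assumed).** If refusers lie Δ SD from the other children in the outcome and a share r refuses, the retained children's mean lies r × Δ from the mean of the whole arm. A complete-case difference between arms therefore shifts by Δ × (r_i − r_c).

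- 10-point gap: 0.25 × 0.10 = 0.025 SD; 0.5 × 0.10 = 0.05 SD. That is 5% to 11% of 0.47.
- 15-point gap: 0.25 × 0.15 = 0.0375 SD; 0.5 × 0.15 = 0.075 SD. That is 8% to 16% of 0.47.
- Equal refusal in both arms: no shift.

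The sign depends on which arm loses more children and on how those children differ. The documents settle neither.

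**Step 5. Asking before allocation.** Consenting families needed for 127 randomised dyads = 127 / (1 − r): 134 at 5% refusal, 142 at 10%, 159 at 20%. The randomised target stays at 127.

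**The case against.** The strongest objection is that this rests on silence. The article is a condensed account, its enrolment flowchart is not visible, and Ethical Considerations reports committee approval. A child assent procedure may well stand in the full protocol or the ethics file. A parent can also ask the child before signing up, and the medical exclusion refers to what either member reported, so some involvement of the child in screening is not ruled out. This stands against any claim that assent is missing or that refusal can surface only after allocation. It does not remove the order that the article states: enrolment on the parent's consent, randomisation at sign-up, baseline and the child's link afterwards.

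A second objection is that declining sessions is not the same as withholding data. A child who skips the video calls may still complete surveys and wear the device. Under the planned intention-to-treat analysis that is non-adherence, which would tend to dilute an effect. This also stands. The bias in Step 4 needs outcome data to be missing, and a refusal at first contact can differ by arm only if the allocation is known by then, which the article does not say.

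A third objection is that screening for agreement removes reluctant children, whom the intervention hopes to reach through training parents in autonomy support, and that a page completed at home with the parent present is a weak test of willingness. Both are fair costs of the fix. Neither is a reason to learn of a refusal after allocation rather than before it.

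**Conclusion.** The point holds as a weakness in the order of events. Followed as written, an unwilling child can be lost after allocation with no child-reported data, and such losses could be unequal because only one arm asks the child to attend sessions.

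The size is unknown. Under assumed gaps of 10 to 15 percentage points in refusal and 0.25 to 0.5 SD in outcome, the shift in a complete-case comparison is 0.025 to 0.075 SD, or 5% to 16% of the planning effect, so it is probably modest. The attrition allowance can cover the numbers but does not correct an unequal loss.

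A reader might infer more, and the documents do not support it:

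- **That children take part without their agreement.** Assent is not mentioned in the article, but nothing says that it is not sought.
- **That the parent's consent makes a dyad eligible.** Eligibility rests on age, activity and health.
- **That the bias favours the intervention.** No refusal rate, arm difference or direction is given.
- **That the Limitations section contrasts a motivated parent with an unmotivated child.** It expects consenting parents to be somewhat motivated and does not describe the child's motivation.

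**What to change.** Amend Trial Design and Study Procedures so that a dyad is randomised only after the child's own agreement is recorded. The existing Webropol sign-up survey can carry a short page addressed to the child that describes both arms (sessions, surveys, accelerometer) and records yes or no. Preferably, randomise only after both members have also completed the baseline survey, so that every randomised child has at least one self-reported measurement. If the child's agreement is already obtained before allocation, one sentence in Study Procedures saying so settles that part.

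The cost is one extra survey page, allocation that waits for the child's answer and preferably the baseline survey, some sign-ups lost before randomisation (Step 5 gives the range under assumed rates), and a child sample slightly more willing than the population aimed at. The target N does not change. The change moves avoidable losses ahead of allocation; it will not prevent later dropout caused by the burden of the sessions.

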#### Waitlist Control Group

Participants assigned to the waitlist control group will complete the same data collection procedures as the immediate intervention group but will not be required to undertake any alternative intervention tasks during the data collection period. After the data collection period, participants in the waitlist control group will be invited to receive the intervention and accompanying materials.

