#### Primary Outcomes (Physical Activity and Sedentary Time)

Self-reported physical activity and time spent in sedentary activities for both parents and children will be assessed using the Godin-Shepard leisure time exercise questionnaire [41], where participants will be required to report the number of occasions they engaged in light, moderate, and vigorous physical activity for 15 minutes or longer. Sedentary time will be measured using 2 items per participant, targeting weekdays and weekend days separately (eg, “In the past 7 days, how much time did you spend sitting during a typical weekday after school or weekend day?”) [42]. Items are scored on a sliding scale from “no time” upwards in increments of half an hour.

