### Data Analysis

Hypotheses will be tested using R software. All analyses will initially be performed as intention-to-treat, and per-protocol analyses will also be undertaken for comparison. Patterns of missing data will be explored using the Little missing completely at random test. Missing data in the final analysis will be inferred using full-information maximum likelihood analysis. We will test the efficacy of the intervention on our primary outcome, self-reported leisure-time physical activity, using an iterative series of generalized linear models. Independent variables will include time, intervention condition, demographic covariates (eg, start date, gender, and age), delivery group clustering, within-dyad clustering, and person-intervention theory fit *P*Δ [51]. Each variable group will be added in a subsequent iteration of the model, and model fit statistics will be examined at each iteration. This process will be repeated for each secondary outcome variable (perceived autonomy support, autonomous motivation, attitude, subjective norm, perceived behavioral control, action planning, coping planning, self-monitoring, and behavioral automaticity).

We also intend to assess the effect of theory-based mediators on change in physical activity using a path model. Specifically, we aim to assess whether the effects of intervention conditions on change scores in physical activity outcomes (both primary and secondary) are mediated by change scores in each of the psychological constructs targeted by the intervention (ie, perceived autonomy support, autonomous motivation, attitude, subjective norm, perceived behavioral control, action planning, coping planning, self-monitoring, and behavioral automaticity).

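### Dyads are randomised before baseline is collected, and nothing says allocation is withheld until baseline is complete, so the self-reported baseline could differ by arm

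*Protocol article*

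**What the plan says.** Trial Design puts randomisation at sign-up and baseline after it: "Families will be randomized on sign-up to either an intervention group that receives the intervention immediately after baseline data collection". Study Procedures gives the same order. First, "After enrolling in the trial, dyads will be assigned by computerized random-digit generation to 1 of 2 groups"; then, "Participants in both groups will be asked to provide outcome data immediately after randomization, 3 months later, and 6 months later". No section places baseline before assignment, and none says that the result of the assignment is held back until baseline is in.

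The control families wait and "will not be required to undertake any alternative intervention tasks during the data collection period". The primary outcome is a questionnaire: "Self-reported physical activity and time spent in sedentary activities for both parents and children will be assessed". The accelerometer, a secondary outcome, is mailed to the home with a wear diary, so its baseline is also recorded after randomisation.

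Under Data Analysis, the terms of the primary models are listed as "Independent variables will include time, intervention condition, demographic covariates (eg, start date, gender, and age", followed by clustering and theory-fit terms. The path model asks "whether the effects of intervention conditions on change scores in physical activity outcomes (both primary and secondary) are mediated by change scores" in the psychological constructs.

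**The concern.** A baseline is a safe reference when it cannot depend on allocation. Measuring it before randomisation guarantees this; concealing the result until it is measured achieves much the same. The article describes neither safeguard.

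This trial is more exposed than most. A family told to wait knows it is the control. Nearly all measures are self-reported, and parents may help their child understand the items, so a parent's knowledge of allocation can reach both questionnaires. Posting and wearing the device takes time, and immediate-intervention families must be ready for live sessions soon after baseline, so early disclosure is plausible.

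Two things are at stake. A baseline that differs by arm because of allocation would bias contrasts that use it, in either direction. A bias towards no effect would also matter for the rule in Study Procedures that cancels the 6-month collection if no effect is seen at 3 months. Separately, families disappointed by allocation may leave before giving any data.

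**Working it through.** **1. Sequence.** Reading Trial Design and Study Procedures together gives: screening and consent, enrolment, assignment, baseline surveys and device, then intervention (immediate arm) or waiting. The two sections agree, so the order is stated and not inferred. The moment of disclosure is not stated.

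**2. What disclosure could alter.** The sedentary-time item refers to the past 7 days. If it is answered promptly, that period lies largely before assignment, so disclosure could change how families report but hardly what they did. The recall window of the activity questionnaire is not given in the article. The accelerometer records days after assignment, so both behaviour and wear could change.

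**3. The plan's own figures (Power Analysis).** Planned effect: (0.45 + 0.48)/2 = 0.465 SD. Half of this is 0.2325; the stated f = 0.235 corresponds to 0.47. A noncentral F calculation with f = 0.235, α = 0.05, power 0.80 and 2 numerator degrees of freedom returns 178. Attrition: 178/0.70 = 254.3, stated as 254, or 127 dyads. This point disputes none of these figures; they serve as the yardstick.

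**4. Bias from a baseline shift.** Let s be the between-arm baseline difference caused by disclosure (in SD), r the baseline to follow-up correlation, n the number per arm, and the true effect zero. The documents give neither s nor r; s = 0.1 to 0.2 and r = 0.5 to 0.7 are assumptions.

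- Change score: |bias| = s; SE = √(2(1−r)) × √(2/n).
- Baseline-adjusted (ANCOVA): |bias| = r × s; SE = √(1−r²) × √(2/n).
- Follow-up only: bias = 0.

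Example with n = 89, s = 0.2, r = 0.5: SE of change = 1 × √(2/89) = 0.150; 0.2/0.150 = 1.33; two-sided rejection rate about 27%.

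With n = 89 per arm (178 observations treated as independent):

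| s | r | Change bias (share of 0.465) | False-positive rate | Adjusted bias (share) | False-positive rate |
|---|---|---|---|---|---|
| 0.1 | 0.5 | 0.10 (22%) | 10% | 0.05 (11%) | 7% |
| 0.1 | 0.7 | 0.10 (22%) | 14% | 0.07 (15%) | 10% |
| 0.2 | 0.5 | 0.20 (43%) | 27% | 0.10 (22%) | 12% |
| 0.2 | 0.7 | 0.20 (43%) | 41% | 0.14 (30%) | 26% |

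With 44.5 per arm (parents or children alone), the change-score rates are 8–9% for s = 0.1 and 16–23% for s = 0.2. With s = 0 every rate is 5%.

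**5. Loss before baseline.** If 5% to 10% of dyads withdrew completely between assignment and baseline (an assumption), that would be 127 × 0.05 = 6.35 to 127 × 0.10 = 12.7, or about 6 to 13 dyads with no outcome at any time.

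**The case against.** The strongest reply is that assignment and disclosure are different events, and only disclosure can alter a report. A computer may assign dyads at sign-up without anyone being told. The flow diagram (Figure 1) was not available to this review, and a condensed article may leave the timing of the message to the full protocol. This stands: a reader might infer that families know their group at baseline, but the documents do not say so. They leave it possible.

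Second, a reader might infer that the primary result is biased one-for-one and that every change score is distorted. The documents do not support that. Change scores are specified for the mediation path model. The primary analysis is a series of generalized linear models with time and condition, and the article does not say how baseline enters. An unconstrained time-by-condition contrast carries the full shift, an adjusted analysis carries r times the shift, and a follow-up-only comparison carries none.

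Third, the loss argument has limits. A dyad that misses only the baseline survey can still give 3-month data, which full-information likelihood can use; only complete withdrawal leaves nothing. The 30% attrition allowance partly covers the numbers. Loss that differs by arm would not be covered, but the documents give no evidence that it occurs.

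Fourth, the workshops are delivered in groups, so early assignment may help to form them. That could justify the order, but not early disclosure.

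What survives is that the stated order creates the exposure and no stated safeguard closes it.

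**Conclusion.** The point holds in conditional form. Randomisation before baseline is explicit. That allocation is known at baseline is not; it is an open possibility in a trial that cannot mask its comparison and relies on self-report. If families are told early, the path model and any contrast measured from baseline could be biased by up to the size of the shift. Under the assumed 0.1 to 0.2 SD that is 22% to 43% of the planned 0.465 SD, or 11% to 30% after baseline adjustment with r between 0.5 and 0.7. The direction is unknown: a real effect could be exaggerated or hidden. Complete withdrawals before baseline would add a gap in the intention-to-treat comparison of unknown size. If allocation is in fact withheld until surveys and device wear are complete, the reporting bias largely disappears and one sentence in the protocol settles it. This is something that should be fixed, and not a demonstrated bias in the primary result.

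**What to change.** Randomise each dyad only after both baseline surveys and the accelerometer wear period are complete. If early assignment is needed to form workshop groups, keep it but withhold the allocation message until that point, and say so under Study Procedures. If this is already the practice, state it.

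For dyads already told their group before completing baseline, record a flag and add a sensitivity analysis that compares follow-up scores without using their baseline. Report by arm how many randomised dyads gave no outcome data at all.

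The cost is a short delay to randomisation, some inconvenience in scheduling delivery groups, and a notification to the ethics committee. Sample size, measures and intervention content do not change. The follow-up-only sensitivity analysis is generally less precise than a baseline-adjusted one, which is acceptable for a supporting analysis.

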## Results

The project team received final notification of research funding approval for the current project from the Finnish Ministry of Education and Culture, Sport Science Funds, in March 2022 (PROJECT 350904), and the trial has been preregistered on ClinicalTrials.gov (ID 806/13.00.04.00/2023). Enrollment into the trial commenced on September 20, 2023. Enrollment is scheduled to continue until March 2024, with the final collection of follow-up data scheduled for December 2024.

We expect that the research will provide valuable formative evidence for the efficacy of a theory-driven family-based physical activity intervention strategy. Further, as the proposed trial includes open materials and tests of the theory-driven mechanistic effects that may encourage behavior change, this research may also serve as a valuable stepping stone to the development of more large-scale, low-cost interventions for family behavior change.

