## Discussion

### Overview

This protocol presents a randomized controlled trial aiming to increase physical activity levels in inactive parent-child dyads within Finland, based on the integrated behavior change model. We hypothesize in this protocol that both parents and children will show increased levels of physical activity, our primary outcome variable, both at the immediate and 3-month postintervention stage, relative to a waitlist control group. Further, we hypothesize we will observe similar changes in the trial’s secondary outcomes, the psychological constructs of the integrated behavior change model (ie, autonomy support, autonomous motivation, attitude, subjective norm, perceived behavioral control, self-monitoring, intentions, and habit), in the intervention group relative to the waitlist control group.

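### The rule that cancels 6-month data after a null 3-month result cannot be applied to the whole cohort under the stated enrolment calendar, and it can drop a hypothesised time point when the intervention works

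*Protocol article*

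**What the plan says.** Under Trial Design: "Families will be randomized on sign-up to either an intervention group" or to a waitlist. Under Study Procedures, both groups are "asked to provide outcome data immediately after randomization, 3 months later, and 6 months later". The same section adds a stopping rule: "6-month follow-up data will not be collected if there is no effect of the intervention on the primary outcome", leisure-time physical activity, at the 3-month follow-up.

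The Results section gives the calendar: "Enrollment into the trial commenced on September 20, 2023", and "Enrollment is scheduled to continue until March 2024, with the final collection of follow-up data scheduled for December 2024".

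The Overview in the Discussion states the hypothesis for each role: "both parents and children will show increased levels of physical activity, our primary outcome variable". It expects this gain over the waitlist group at two stages, "both at the immediate and 3-month postintervention stage". The second of these stages is the 6-month visit. The primary outcome at 6 months is therefore a hypothesised result, not an optional extra.

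**The concern.** The rule presupposes a moment when the 3-month result is known and no 6-month data have yet fallen due. With about six months of rolling enrolment and a three-month gap between the two visits, that moment does not exist. Whoever applies the rule must either wait until much of the cohort has passed 6 months or decide on incomplete 3-month data.

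The rule can also remove the maintenance hypothesis because of a false negative at 3 months. Visits not made cannot be recovered. If the 6-month data exist only because the 3-month result was favourable, the 6-month estimate is a selected one.

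**Working it through.** **1. Calendar.** Inputs (Trial Design, Study Procedures, Results): first enrolment 20 September 2023; last enrolment between 1 and 31 March 2024; visits at 0, 3 and 6 months from each family's randomisation. Assumption: uniform accrual.

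- First 6-month visit: about 20 March 2024.
- Last 3-month visit: 1 to 30 June 2024.
- A dyad passes 6 months before the last 3-month visit if it enrolled at least three months before the last dyad.
- Last enrolment 1 March: enrolled by 1 December = 72 of 163 days = 44%, about 56 of 127 dyads.
- Last enrolment 31 March: enrolled by 31 December = 102 of 193 days = 53%, about 67 of 127 dyads.
- 3-month data in hand on 20 March 2024 come from dyads enrolled by 20 December 2023: 91/193 = 47% to 91/163 = 56%.

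In general the overlap is (enrolment span − 3 months)/span. A constant delay before baseline does not change it. It vanishes only if all baselines fall within three months.

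**2. The plan's own sample size.** Power Analysis gives f = 0.235, α = .05, power .80, N = 178, then 254 recruited. Noncentral F with λ = f²N = 0.235² × 178 = 9.83 gives power 0.801 with 2 numerator degrees of freedom, so 178 reproduces on that basis. A two-arm contrast with 1 degree of freedom would need 145. Attrition: 178/0.70 = 254.3. By the plan's own statement, the chance of a non-significant result when the effect is real is 1 − 0.80 = 20%.

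**3. False-stop risk on full 3-month data.** Assumptions: no effect means p≥.05 two-sided; 1:1 allocation; true d = (0.45 + 0.48)/2 = 0.465, from the two effect sizes in Power Analysis. Noncentral t, with noncentrality d√(N/4) for N independent people. For dyad means with within-dyad correlation ρ, d is replaced by d/√((1+ρ)/2) and N by the number of dyads. At ρ = 0.3, 0.465/√0.65 = 0.577.

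| Test at 3 months | Noncentrality | Risk of wrongly stopping |
|---|---|---|
| Pooled, 178 people, independent | 0.465 × √44.5 = 3.10 | 13% |
| Pooled, 89 dyads, ρ = 0.3 | 0.577 × √22.25 = 2.72 | 23% |
| Pooled, 216 people (15% lost by 3 months, assumed), independent | 0.465 × √54 = 3.42 | 7.5% |
| Pooled, 108 dyads (15% lost), ρ = 0.3 | 0.577 × √27 = 3.00 | 16% |
| Parents alone or children alone, 89 people | 0.465 × √22.25 = 2.19 | 42% |

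**4. Selection.** At 80% power the noncentrality is 1.96 + 0.84 = 2.80. Conditional on significance its mean is 2.80 + φ(0.84)/0.80 = 2.80 + 0.35 = 3.15, so the 3-month estimate is inflated by about 12%. At 87% power the figure is about 8%; at 59% power (one role alone) about 30%. These apply to the 3-month estimate. If r is the correlation between the 3- and 6-month estimates, the 6-month estimate is shifted by r × 0.35 standard errors at 80% power. The document gives no r.

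**The case against.** **The rule could still do something.** It could cancel visits for dyads not yet due, so it is not wholly inoperable. This stands: the claim is only that it cannot be applied to the whole cohort as written.

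**The percentages are assumptions.** Sessions run in groups, so starts may be batched. The last follow-up is given as December 2024, whereas March enrolment plus six months ends in September. Both points are fair. But batching removes the overlap only if every baseline falls within three months, which randomisation on sign-up does not provide for. If December implied enrolment to June 2024, the overlap would rise to about 68%.

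**A gate is legitimate.** Asking about maintenance only after an initial effect is a recognisable prespecified choice. Applied after all 3-month data are in, it leaves the 3-month comparison and its type I error intact. It also spares unpaid families some burden and could shorten the waitlist. That stands as a reason for wanting a rule, but does not reconcile this one with the calendar or the 6-month hypothesis.

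**Stronger readings the documents do not support:**
- *Autumn enrollees confound the effect with season.* Both arms are randomised concurrently, so they share the season. Precision and generalisability suffer; the between-arm comparison does not.
- *The rule misfires about half the time.* That would require a decision on roughly half of the data around 20 March 2024, a look no section describes.
- *The test, threshold and population for judging no effect are missing.* These may sit in a full protocol or analysis plan not shown.
- *The budget already covers full 6-month collection.* The article says only that funding was approved.

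**Conclusion.** The concern holds in a limited form. The stopping rule, the sign-up randomisation and the enrolment dates are incompatible within the article itself: 44% to 53% of dyads reach 6 months before complete 3-month data exist, given uniform accrual and last enrolment in March 2024. An unseen analysis plan could define how no effect is judged, but those definitions would not remove this overlap.

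If the planned effect is real and no effect means p≥.05, the chance of wrongly losing the 6-month time point on full 3-month data is 20% at the stated power. It is about 8% to 23% for a pooled test, with 15% to 30% attrition by 3 months and a within-dyad correlation of 0 to 0.3, and about 42% for one role alone. The attrition by 3 months and the correlation are assumed; adjusting for baseline would lower these risks.

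Upward selection of the 6-month estimate follows if the two time points are positively correlated. Its size cannot be fixed from the document.

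**What to change.** Delete the stopping rule. Collect at least the 6-month web survey, which Study Procedures already plans, from every dyad, and report the 6-month effect whatever the 3-month result.

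If cost is the concern, make only the third accelerometer mailing conditional. Use a pre-stated futility criterion, for example that the upper 95% confidence limit of the pooled 3-month effect lies below a stated smallest effect of interest. Apply it once all 3-month data are in, and say what happens to dyads already past 6 months.

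The cost is a short amendment, survey burden for families whose 6-month visit would otherwise have been cancelled, and a waitlist group that keeps its originally planned start instead of a possible earlier one. If some form of the rule is kept for all 6-month data, Trial Design, Study Procedures, Results and the Discussion overview must be reconciled, with the decision date and the data it rests on stated.
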